### Secondary analysis

We are also interested in the effect of the SRH App among those who download and use the App. Using the data from the app developer, we shall construct a binary index of app use. We shall then conduct an instrumental variables analysis to obtain an estimate of the effect of app use on SRH uptake and awareness. We shall conduct the standardized test to verify whether the instrument has good predictive power in the first stage of the regression and whether it is valid in a multiple regression analysis with the observed characteristics included in the model.

We also further assess if SRH awareness is associated with changes in SRH uptake among the study participants in both arms of the study. We will construct an index for SRH awareness and the conduct a binary regression analysis with SRH uptake as the response variable and SRH awareness as the explanatory variable. We check the validity of the association in a multiple regression analysis with observed characteristics included in the model. Both adjusted and crude odds ratios with their corresponding confidence intervals and *p*-values will be reported. All results will be considered statistically significant at a 5% level of significance.

To assess acceptability and user-satisfaction, we will analyze the download and usability statistics and reviewer comments on the app from those randomized to receive the app. Further, we have included questions on acceptability and user satisfaction (user rating of the app) and will report simple proportions for each question.

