### Baseline and follow-up assessments

Enrolled study participants will be followed up at one and six months to determine the effectiveness of *the* SRH App in increasing SRH awareness and uptake*.* A standardized questionnaire has been developed for this study. At enrollment, the research assistant will obtain background information from eligible and consenting participants. We will collect data on the demographic and socioeconomic characteristics, SRH knowledge, sexual behavior and attitude, and SRH uptake (contraception and sexually transmitted infections testing and treatment). Information on SRH uptake will be self-reported at both baseline and end line. Questions on SRH knowledge and sexual behaviors will be modified from the World Health Organization (WHO) SRH guiding questionnaire [40] and the Uganda AIDS Indicator Survey [11]. Questions on SRH uptake will be obtained from the UDHS questionnaire. The questionnaire will be administered to consenting participants at enrollment. At the close of the study (after un-blinding the GHE (U) Ltd. team), we shall conduct an acceptability and user satisfaction survey among participants in the intervention arm of the study. We will also follow up the recruited participants in the two study arms with the standardized questionnaire similar to the baseline questionnaire to assess the impact of the SRH App on program indicators.

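### The awareness analysis asks about changes in uptake, but its stated response is uptake itself with no baseline uptake named, so it can report an association when awareness is unrelated to any change

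*Protocol article*

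**What the plan says.** The question is in the Secondary analysis section: "We also further assess if SRH awareness is associated with changes in SRH uptake among the study participants in both arms of the study". The next sentence builds an awareness index and proposes to "conduct a binary regression analysis with SRH uptake as the response variable and SRH awareness as the explanatory variable". A further model follows: "We check the validity of the association in a multiple regression analysis with observed characteristics included in the model". The section then commits to reporting "Both adjusted and crude odds ratios with their corresponding confidence intervals", and closes with "All results will be considered statistically significant at a 5% level of significance".

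The section does not define a participant-level change in uptake, does not name baseline uptake as a covariate, does not say at which visit the awareness index is measured, and does not list the observed characteristics.

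The section on baseline and follow-up assessments shows what is available. The enrolment questionnaire covers "SRH knowledge, sexual behavior and attitude, and SRH uptake (contraception and sexually transmitted infections testing and treatment", and "Enrolled study participants will be followed up at one and six months".

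**The concern.** Uptake at a visit and change in uptake since enrolment are different quantities. The Sample size calculation section takes modern contraceptive use among young people as 30.2% before the trial, so a sizeable share of month-six users may simply be people who were users at enrolment. If those students also scored higher on awareness at enrolment, a regression of uptake on awareness picks up that earlier difference and carries it to month six, whether or not anyone's uptake changed. The same happens inside each arm, including the control arm, so adding an arm term would not remove it.

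At stake is how a supporting result is read. Closing the knowledge gap is part of the app's rationale in the Background and Discussion. A significant odds ratio reported under a question about change would look like support for that rationale, when the model cannot separate change from differences that existed before the trial.

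**Working it through.** The plan gives no figure for this analysis, so there is none to reproduce. The check asks how often the stated model is significant at 5% when change in uptake is unrelated to awareness.

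**Inputs from the protocol article**
- Analysed sample: 958 less 10% non-response, 958 × 0.9 = 862, arms pooled.
- Baseline uptake: 30.2%, the modern contraception figure.
- Two-sided 5% level.

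**Assumed, because the document gives no value**
- Baseline odds ratio per SD of awareness: 1.0 to 2.0.
- In the switching scenario, 10% of non-users start, independently of awareness. To hold prevalence constant, the share of users who stop is 0.10 × 0.698 / 0.302 = 0.231.
- In the switching scenario, awareness correlates 0.7 between baseline and month six.

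**Simulation**: 1,000 trials per cell, logistic regression on standardised awareness. Percent of trials with p < 0.05 for awareness:

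| Baseline OR per SD | Nothing changes: stated crude model | Random switching: stated crude model | Random switching: baseline uptake added | Random switching: new uptake among baseline non-users, on change in awareness |
|---|---|---|---|---|
| 1.0 | 4.4 | 3.5 | 3.5 | 4.2 |
| 1.2 | 68.5 | 20.9 | 5.0 | 5.7 |
| 1.3 | 93.0 | 37.7 | 4.5 | 5.4 |
| 1.5 | 100 | 74.3 | 6.1 | 6.3 |
| 2.0 | 100 | 98.0 | 4.1 | 4.9 |

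**Check by hand**
- The standard error of the log odds ratio per SD is about 1/√(N p(1 − p)) = 1/√(862 × 0.302 × 0.698) = 1/√181.7 = 0.0742.
- Nothing changes, OR 1.2: ln 1.2 / 0.0742 = 0.1823 / 0.0742 = 2.46. The chance of exceeding 1.96 is Φ(2.46 − 1.96) = Φ(0.50), about 69%.
- Random switching shrinks the slope by about (1 − 0.10 − 0.231) × 0.7 = 0.468.
- Random switching, OR 1.2: 0.1823 × 0.468 / 0.0742 = 1.15, and Φ(1.15 − 1.96) is about 21%.
- Random switching, OR 1.5: 0.4055 × 0.468 / 0.0742 = 2.56, and Φ(2.56 − 1.96) is about 73%, against 74.3% simulated.

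**Awareness measured at baseline.** The table's baseline-adjusted column uses month-six awareness. A separate run with n = 870 and the same 10% switching regressed month-six uptake on baseline awareness. Without baseline uptake it was significant in 45%, 77% and 100% of trials when baseline users scored 0.2, 0.3 and 0.5 SD higher. With baseline uptake in the model the rate was 4% to 6%.

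**The case against.** Several objections have force.

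- **The text is open, not categorical.** A reader might infer that the plan definitely regresses level on level and excludes baseline uptake. The document does not say that. It gives no visit for the index, and its unlisted observed characteristics could include baseline uptake, a detail often left to an analysis plan. This stands as a limit on the adjusted model. It does not rescue the crude odds ratio, which has no covariates and which the plan commits to reporting.
- **Uptake may be shorthand for the change outcome.** The Study outcomes section does define the primary outcome as a change. But that is a change in a proportion, a group-level quantity. A regression yielding odds ratios needs a binary response for each participant, and no participant-level change is defined.
- **Only association is claimed.** This is correct. A reader might infer that the plan will claim that raising awareness raises uptake, but the section speaks only of association and keeps effect language for the instrumental-variables analysis. The mismatch remains, because the association it names is with changes.
- **The model detects something real.** Under a baseline gap, the test correctly finds that users know more. The error is in treating that as an answer about change.
- **The largest percentages are worst cases.** They need a baseline association and no change at all over six months. With random switching the rates at 1.2 and 1.3 fall from 69% and 93% to 21% and 38%.

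A reader might also infer a sizeable distortion from knowledge gained at the moment of uptake. That is possible if both are measured at the same visit, but its size is not established. If 15% of all participants start and each gains 0.5 SD of knowledge, simulations give 65% to 68% significant. If the 15 points arise only in the app arm, 7.5% of all participants, the figure is 28%.

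**Conclusion.** The point holds as a mismatch between the stated question and the stated model. Followed as written, the analysis describes who uses services, not whose use changed, and its crude odds ratio is unprotected against differences present at enrolment.

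The size is conditional. With no baseline association, the model is significant in about 5% of trials. At assumed baseline odds ratios of 1.2 to 1.5 per SD, it is significant in about 21% to 74% under modest random switching with a 0.7 awareness correlation, and about 69% to 100% if nothing changes. The document supplies none of these assumed values. Students who already knew and already used services can produce such a result; it does not follow that they will.

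This is a supporting, observational analysis. The randomised primary comparison is not affected. The section should be corrected, but the trial's main conclusion does not depend on it.

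**What to change.** Amend the Secondary analysis section in one or two sentences:

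- Define the response as month-six uptake with baseline uptake as a named covariate, or as new uptake at month six among baseline non-users.
- Define the explanatory variable as baseline awareness or change in awareness, and state the visits.
- Report any unadjusted or same-visit odds ratio as a cross-sectional association, not as evidence about change.

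The two explanatory variables involve a trade-off. Baseline awareness settles the time order but leaves out awareness gained during the trial. Change in awareness includes that gain but, measured over the same interval as uptake, leaves direction open.

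No new data are needed, since knowledge and uptake are both collected at enrolment. The cost is a somewhat wider interval and a weaker-looking association. Restricting to baseline non-users would also leave about 862 × 0.698 = 602 participants for contraception, and would say nothing about those who stop.

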### Quality assurance of the SRH App services

We have identified three quality assurance areas for services provided using the app: 1) quality of SRH services and products provided by the clinics and pharmacies, 2) preventing contamination of the tools on delivery, and 3) ensuring that the product is received by the user that ordered for it. We propose to recruit registered and certified clinics and pharmacies to provide the SRH App services. Partner clinics and pharmacies will be recruited by GHE Consulting medical and pharmacy specialists. Product will be delivered in sealed packages. The user will receive the notification that the order has been sent and after receiving it they will confirm and the notification will be sent to the sender that the order has been received. We will also partner with SafeBoda that are identifiable, trackable and promote safety in the bodaboda business in the country. The app will include a live chat feature, allowing users to ask questions and make complaints about services delivery.b)Cost-effectiveness and budget impact analysis

We propose to conduct a model-based incremental cost-effectiveness analysis (CEA) and budget impact analysis (BIA). The main outcomes of the economic evaluation will be the average cost per app user, cost per app service provided, and cost per disability-adjusted life year (DALY) averted. The cost per app user will be stratified distance measured in kilometers. The crude estimate of distance will be estimated by the distance between the health facility and the pickup point. We also propose to perform a static aggregate budget impact analysis (BIA) to examine the potential economic value of scaling up the App services delivery to the government and the individual taxpayer.

We will perform a primary micro-costing of the SRH App services delivery model from both the payer’s perspective, i.e. include all direct medical and all direct non-medical costs, and the modified societal perspective, i.e. add indirect costs of lost productivity as a result of app use. The direct medical costs will include all resources used in providing SRH services in terms of the medical devices and supplies. The direct non-medical costs will include transport costs incurred in delivering the services, communication costs involved, app administration costs, other program costs and the opportunity costs. Data on costs will be collected through the app use statistics and health facility personnel costs.

We will also estimate the aggregate national budget impact as well as the cost per Ugandan taxpayer per year of implementing the SRH app services delivery model. The BIA will involve the following steps: 1) characterization of the population of Uganda to estimate the potential number of people to be impacted by the app, 2) selection of a time horizon between 1 and 3 years, 3) documenting the current state of SRH services demand creation models nationally, 4) estimating the cost of SRH App services delivery model at scale, and 5) presenting budget impacts tailored to different audiences. The main analysis will be the generation of an estimate of the potential annual fiscal implication for the taxpayer and the government.c)In-app advertising

We propose to develop the advertisement interface in the app to test a way of generating revenues to the sustain the subsidies that will be extended to the users of the SRH App. We will develop high-impact pitches and approach the different companies like telecommunication companies, hospitals, and pharmacies, beverage and breweries companies, among others and invite them to buy advertising space in the app. We will develop metrics for cost estimation and content for the different adverts based on the Uganda Communications Commission guidelines and market prices and sell advertising space to corporations.

We will assess companies’ willingness to advertise with the app at scale-up through the key informant interviews. A key informant interview is attached. We will also assess the satisfaction level of app users on the advertisement interface. Satisfaction questions are included in the acceptability and user satisfaction questionnaire.

#### Local regulatory requirements

We do not anticipate any local ICT regulatory requirements either from the Uganda Communications Commission or the Ministry of Information and Communications Technology. However, should these arise we are prepared to present all necessary documentation. We will involve the BCC experts in the Ministry of Health and the IT experts at the National Information Technology Authority (NITA) and we shall share all iterations of the app with both the Ministry, NITA and MUST IRB.

#### Ethical considerations

This study will be submitted for approval by the Mbarara University of Science and Technology (MUST) Institutional Review Board (IRB) and the Uganda National Council of Science and Technology (UNCST). All investigators have or will receive ethics training prior to the start of the study. All participants will provide informed consent and will be allowed withdraw consent at any time. Study documents will be kept under highest standards of confidentiality and records will be kept under lock and key.

This is a data-sensitive project, especially with regard to confidentiality of participants’ mobile phone contact numbers, and SRH service and tools clinical records. We will make every effort to limit access to the client records. We shall discuss possible encryption technologies with the app developer. In any case, it is only the app developer who will have access to telephone numbers, and all records of numbers will be destroyed at the completion of final data collection phase.

The SRH App poses minimal risks to the user. In the event that the user registers any adverse event or side effect as a result of the use of SRH app tools and services, they can make an appointment with our clinic or go to the nearby partner clinic for help. We will report any such cases to MUST review board within 7 days of the occurrence.

#### Study status

The study has already hired an experienced app developer, conducted the first set of Focus Group Discussions, and the app prototype is currently under development.

## Discussion

In this pilot study, we will develop a sexual and reproductive health services delivery and awareness phone application and assess its effectiveness in increasing awareness and uptake of sexual and reproductive health services among the youth aged 18 to 30 years using a randomized controlled design. The study will also assess the acceptability, usability, cost-effectiveness of this services delivery model. Further to this, the study will also assess effectiveness of in-app advertising as a way of generating revenues possible transition to scale. Existing evidence reveals that sexual and reproductive health programs tailored to the youth should be accessible, equitable, appropriate and effective [17]. The challenges affecting the youth and adolescents in low-income nations like Uganda include privacy, confidentiality, and limited SRH knowledge [11]. We hypothesize that the proposed App that will allow the youth to order for SRH tools and have them delivered to their preferred pick-up points presents an a private, confidential, youth-friendly and effective method of creating demand for sexual and reproductive health tools among the youth. The App will also enable the users to book for the services online from a pool of the partner clinics, and also have access to sexual and reproductive health information tips. The intervention provides subsidies inform of price cuts on the products and services to further incentivize the low-income youth to embrace safe sexual practices, increase use of family planning services, and other sexual and reproductive health services. Thus, our innovation reduces both the knowledge and financial barriers to access of SRH information and services by providing comprehensive SRH information and subsidizing SRH services. In the long run, the SRH App will be self-sustaining through revenues from in-app advertisements. The study helps in understanding 1) the causal effect of mobile phone applications and SRH service demand creation and uptake among youth age 18–30, 2) the cost-effectiveness of such interventions in low-income settings, and 3) the use of in-app advertisements for revenue generation to SRH services. If the study is successful, it will present policymakers and other stakeholders in Uganda, and internationally, with a viable services delivery model for increasing uptake of SRH services, tools, and awareness among the youth. The strength of this study lies in it’s innovativness to leverage mobile phones to provide the non-existent servics delivery model in the line of sexual and reproductive health services. The further applies a rigorous study design-a randomized controlled study design to evaluate the effcetiveness of the App. Even though the study is controlled, we are not able to control students in the control group interacting with with students in the trial arm of the study. This has potential for bias and a possibility of App services mis-use for tools that will be ordered online.

## Conclusion

This paper has described the steps that will be taken to develop and evaluate the impact of mobile phone application in increasing awareness and uptake of SRH services among the youth in Uganda. Unlike existing non-self-sufficient programs, this study will provide evidence on the use of in-app purchases as a means of funding the transition to scale. The pilot study will culminate into a demand-driven, culturally-relevant, and easy-to-use mobile app that will be popularly used and effective among the youth in Uganda.

## Abbreviations

ATE: Average treatment effect
BIA: Budget impact analysis
CEA: Cost effectiveness analysis
DALY: Disability adjusted life years
DID: Difference in difference
FGDs: Focus Group Discussions
GCC: Grand Challenges Canada
GHE: Global Health Economics
HIV: Human immune virus
IRB: Institutional review board
ITA: Intention to treat analysis
KYU: Kyambogo University Uganda
LMICs: Low and middle-income countries
MUST: Mbarara University of Science and Technology
NITA: National Information Technology Authority
ODK: Open data toolkit
SDGs: Sustainable Development Goals
SRH: Sexual and reproductive Health Services
STI: Sexually Transmitted infections
UDHS: Uganda Demographic and Health Survey
UNCST: Uganda National Council of Science and Technology
WHO: World Health Organization
